### Study centres and recruitment

Participants are recruited from sheltered housing facilities at three mental health care organisations in the Northern Netherlands: Cosis, GGZ Friesland, and Lentis Psychiatric Institute. Recruitment involves collaboration with healthcare professionals at these institutes, who help identify potential participants and organise informative meetings. Eligible participants receive detailed oral and written information about the study and have at least one week to decide. Written informed consent is obtained before participation, and participants may direct any further questions to the researchers. Participants are informed about the randomised trial design, emphasising that group assignment is random and that improvement in goal attainment, daily functioning, or cognition cannot be guaranteed. Retention is promoted by maintaining regular contact with participants during the waitlist period, offering flexibility to accommodate participants’ preferences, and emphasising the potential benefits of the training. Withdrawal is possible at any time without consequences.

After completing the training, participants are invited to participate in an additional in-depth interview. They receive the same informed consent procedure and detailed information (i.e., time to consider participation, questions, consent, and withdrawal) only if they express interest. Researchers or CIRCuiTS therapists invite participants during or after the final training session.

### Randomisation and blinding

Participants are randomly assigned in a 1:1 ratio to either active or sham stimulation, using a computer-generated randomisation plan with permuted blocks of varying, undisclosed sizes to ensure allocation concealment. An independent researcher, not involved in any aspect of the trial, links the randomisation codes to the corresponding tDCS conditions and implements the allocation procedure. Consequently, both researchers and participants remain blinded to the stimulation condition. Neuropsychological test assessors, who hold at least a propaedeutic psychology degree and are trained in assessment, are also blinded and unaware of the study’s design and purpose. To evaluate blinding, assessors indicate after every assessment their perception of the study’s aim and the participant’s allocation (“Experimental,” “Control,” “No control or experimental condition,” or “I do not know”). After 16 sessions and upon intervention completion, participants and therapists report whether they believe active or sham stimulation was received. The actual treatment allocation will be disclosed only after the last participant completes the T3 assessment. During the trial, unblinding is permitted only if necessary to protect the participant’s health and safety.

### Interventions

CR and tDCS are delivered individually, twice weekly for 16–20 weeks, equating to 32–40 sessions. Given that missed sessions may occur over this period, intervention completion is defined as attending at least 20 sessions, in line with the developers’ recommendations [44]. Each session lasts 30–45 min, depending on the participant’s attention span, with tDCS applied concomitantly during the first 20 min of CR. Therapists determine the total number of sessions required based on individual progress and needs. Missed sessions are not rescheduled. Before, throughout, and after the study, participants continue to receive treatment as usual, including therapies and activities such as cognitive behavioural therapy, creative therapy, or psychomotor therapy tailored to each individual’s needs.

#### Cognitive remediation

The CIRCuiTS programme [44] employs a village metaphor and targets cognitive practice, strategy use, and metacognitive engagement. Tasks focus on attention, visual and verbal memory, and planning, and progress from abstract exercises to more complex, ecologically valid tasks, such as writing text messages or planning bus journeys. The programme and therapists suggest problem-solving strategies, track, evaluate, and discuss progress with participants. Therapists encourage monitoring and regulation of cognitive performance to foster metacognitive engagement and transfer of learned skills to everyday life. CIRCuiTS facilitates metacognitive awareness, encompassing (1) metacognitive knowledge, understanding one’s cognitive strengths and weaknesses, recognising optimal performance conditions, and implementing strategies for improved memory retention, and (2) metacognitive regulation, evaluating and adjusting this knowledge [33]. The therapy is personalised to align with the participant’s goals and performance.

Therapists, such as psychologists, rehabilitation coaches, and others with related expertise, must complete the official CIRCuiTS training programme (https://www.circuitstherapyinfo.com/training) before administering it. They receive weekly supervision from an experienced CIRCuiTS therapist during the first three months, gradually decreasing as proficiency in delivering the treatment develops, alongside monthly supervision from a clinical psychologist. This supervision ensures that therapists support participants appropriately and adhere closely to the intervention protocol.

#### Transcranial direct current stimulation

TDCS is administered using an Eldith DC stimulator (NeuroConn) targeting the DLPFC. The anode is positioned at Fp1 and the cathode at C3, following the 10–20 system, based on computational modelling with SimNIBS software [67]. Simulation results are presented in the supplementary material. Rubber electrodes (5 × 5 cm, 25 cm2) are secured with conductive paste (Ten20^®^, Weaver and Company, Aurora, CO, USA), maintaining impedance below 50 kΩ. Active stimulation consists of a 2 mA current for 1200 s, including a 30-second fade-in/out, concurrent with the first 20 min of cognitive training. This duration follows evidence suggesting that prolonged stimulation may not enhance effects [68]. In the sham procedure, the fade-in is followed by a 30-second fade-out with standard control pulses that have no therapeutic effect, to monitor electrical conductivity.

### Assessments

The researcher (NB) administers all baseline measures and sets goals with participants, test assessors administer the primary and secondary outcome measures, and a member of the research team conducts the in-depth interview.

#### Baseline measures

##### Demographic and clinical characteristics

 Baseline data include year of birth, gender, education level, primary and comorbid diagnoses, medication use, alcohol and drug use, age at first hospitalisation, and other relevant medical events or disorders.

##### Severity of clinical symptoms

 Positive, negative, and general psychiatric symptoms are assessed using the Positive and Negative Symptom Scale – brief (PANSS-6), a validated short version of the PANSS [69–72]. The PANSS-6 is developed to provide a typological and dimensional characterisation of schizophrenia, comprising six items scored on a 7-point scale, with higher scores indicating greater symptom severity. The scale includes three positive symptoms items (delusions, conceptual disorganisation, and hallucinations) and three negative symptoms items (blunted affect, social withdrawal, lack of spontaneity and flow of conversation).

##### Treatment expectancy

 Participants rate their expectations of the intervention’s effectiveness on a 1–10 scale, with 1 indicating no expected improvement and 10 indicating strong expected improvement.

#### Primary outcome measures

##### Goal attainment

 The Goal Attainment Scale (GAS) is a structured measure designed to capture self-reported recovery goals [73] and has been widely applied in research and rehabilitation practices [74–77]. Unlike trials relying solely on global outcomes, the GAS allows for a more pragmatic assessment of CR by evaluating the impact and effectiveness on individualised, real-world goals. Participants define up to a maximum of three individual recovery goals during an interview. Each goal is scored between − 2 and 2, with higher scores indicating better performance, and weighted according to importance and difficulty. Evaluations occur at subsequent assessments using a GAS-weighted T-score derived from recent research methods [78] and approaches used in a large CIRCuiTS trial [77].

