### Participant timeline

An overview of enrollment, intervention, and assessments is shown in Table 1.

**Table 1 Tab1:** Schedule of enrolment, interventions, and assessments

Timepoint	Enrolment	Pre-intervention		Intervention	Post-intervention	6-months follow-up
	< T_0_	T_0_	T_1_		T_2_	T_3_
Enrolment						
Eligibility screen	x					
Informed consent	x					
tDCS safety checklist	x					
Randomisation						
Allocation			x			
Interventions						
CR + active tDCS				x		
CR + sham tDCS				x		
Assessments						
PANSS-6		x				
GAS		x (goals set)	x (outcome rated)		x (outcome rated)	x (outcome rated)
ILSS-I & -SR		x	x		x	x
COWAT		x	x		x	x
TMT-A & -B		x	x		x	x
BADS key search		x	x		x	x
WMS-IV visual reproduction		x	x		x	x
Digit Span (forward/backward)		x	x		x	x
WT-15		x	x		x	x
SCWT		x	x		x	x
CFQ		x	x		x	x
DEX-S & -I		x	x		x	x
NOSCA		x	x		x	x
SNS		x	x		x	x
GSES		x	x		x	x
SFS		x	x		x	x
Behapp		x	x		x	x
In-depth interview					x	

*BADS* Behavioural Assessment of the Dysexecutive Syndrome, *CFQ* Cognitive Failure Questionnaire, *COWAT* Controlled Oral Word Association Test, *CR* cognitive remediation, *DEX−S & −I* dysexecutive questionnaire – self & informant, *GAS* Goal Attainment Scale, *GSES* General Self−Efficacy Scale, *ILSS−I & −SR* independent living skills survey – informant & self−report, *NOSCA* nurses’ observational scale of cognitive abilities, *PANSS−6* The Positive and Negative Syndrome Scale – brief, *SCWT* Stroop Colour and Word Test, *SFS* Social Functioning Scale, *SNS* self−evaluation of negative symptoms, *tDCS* transcranial direct current stimulation, *TMT* Trail Making Test, *WMS−IV* Wechsler Memory Scale – Fourth edition, *WT−15* 15−word learning task

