### Statistical analysis

Data analyses will follow an intention-to-treat approach using multilevel models implemented in R (‘lme4’ or ‘glmer’ packages). This approach accounts for the nested structure of repeated measures within participants and participants nested within centres. Model assumptions will be assessed using scatter plots of residuals and Quantile-Quantile (QQ) plots. Multilevel models are generally robust to moderate violations of normality. Models will be estimated using maximum likelihood, which uses all available data under a missing-at-random assumption.

We will build separate multilevel models for each primary and secondary outcome. Timepoint will be included as a categorical within-subject variable with four levels (T0 = baseline; T1 = pre-intervention; T2 = post-intervention; T3 = follow-up). Centre and tDCS condition (active vs. sham) will be included as between-subject variables. Given the staged recruitment, cohort will be included as a fixed-effect covariate to account for cohort-related differences over time (e.g., staff changes or evolving site practices). Models will include a random intercept for baseline differences across individuals, and, where supported, a random slope for timepoint will allow individual trajectories over time (simplified if convergence issues arise). Fixed effects will be estimated for timepoint, tDCS condition, centre, cohort, and their relevant interactions. We will set T1 (pre-intervention) as the reference level to be able to compare T0 vs. T1 (changes during waitlist period), T2 vs. T1 (changes during intervention), and T3 vs. T1 (longer-term changes).

The primary CR effect will be evaluated by comparing changes observed during the intervention period with changes during the waitlist period, pooling across tDCS conditions. The tDCS augmentation hypothesis will be tested via the intervention × timepoint interaction, operationalised as the difference in change from T1 to T2 and from T1 to T3 between active tDCS and sham tDCS. Given the trial is powered for the primary within-subject CR effect rather than the between-group tDCS contrast, tDCS results will be interpreted as secondary and hypothesis-generating, emphasising effect size estimates and 95% confidence intervals.

We have three primary outcomes (GAS, ILSS-O, ILSS-SR). To control multiplicity, we will control the family-wise Type I error rate across the three primary outcomes at two-sided α = 0.05 using the Holm correction.

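### GAS is a primary outcome with no rating scheduled at T0, so the waitlist-controlled contrast defined for every primary outcome cannot be estimated for it as written

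*Protocol article*

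**What the plan says.** **Status of GAS.** The Statistical analysis section states "We have three primary outcomes (GAS, ILSS-O, ILSS-SR") and controls the family-wise error across the three with Holm at two-sided 0.05. The Discussion refers to GAS, in the singular, as the primary outcome.

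**When GAS is scored.** Under Goal attainment, participants define up to three goals in an interview. "Each goal is scored between − 2 and 2, with higher scores indicating better performance", with weights for importance and difficulty. Then: "Evaluations occur at subsequent assessments using a GAS-weighted T-score". In Table 1 the GAS cell at T0 is annotated as goal setting, while the cells at T1, T2 and T3 read "x (outcome rated"). The other outcomes followed from T0 to T3 carry a plain mark at all four visits. The Assessments section also separates the two acts: the researcher sets the goals, and test assessors administer the outcome measures.

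**How it is to be analysed.** "We will build separate multilevel models for each primary and secondary outcome". Timepoint has four levels, T0 to T3, with T1 as reference. The first comparison listed is "T0 vs. T1 (changes during waitlist period"). The primary CR effect is obtained by "comparing changes observed during the intervention period with changes during the waitlist period, pooling across tDCS conditions". No other contrast is given for GAS.

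**The concern.** The design's claim to internal validity rests on the 16-week wait serving as each participant's comparator. For that, an outcome has to be scored at both ends of the wait. GAS, on the stated schedule, is scored only at the end.

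Faced with this at analysis, a statistician has two ways out, and the article sanctions neither. One is to drop T0 and report T2 versus T1. That is a before-after change which includes whatever would have happened without CR, yet it would sit in a family of tests presented as waitlist-controlled. The other is to supply a T0 value after the fact, in which case the value chosen becomes part of the estimated effect. Either decision would be taken on a confirmatory outcome after the data had been collected.

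**Working it through.** The plan gives no figure on this point to reproduce; the sample size calculation concerns daily functioning, not GAS. The check sets the scores that the contrast needs against the scores that the schedule supplies.

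**Step 1: the contrast.** Intervention change minus waitlist change:

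(T2 − T1) − (T1 − T0) = T2 − 2·T1 + T0.

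It needs a score at T0, T1 and T2.

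**Step 2: what Table 1 supplies.**

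| Outcome | T0 | T1 | T2 | T3 | T2 − 2·T1 + T0 |
|---|---|---|---|---|---|
| ILSS self-report | scored | scored | scored | scored | estimable |
| ILSS informant | scored | scored | scored | scored | estimable |
| GAS | goals set, no rating | rated | rated | rated | not estimable |

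**Step 3: can the model recover it?** The article relies on maximum likelihood under missing at random. That borrows information from participants who do have the score. Here no participant has a scheduled T0 rating, so the T0 level of the time factor has no GAS data and its coefficient is not identified.

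**Step 4: what remains for GAS.** T2 versus T1 and T3 versus T1 can be estimated. So can the difference between active and sham in those changes, which is how the article defines the tDCS hypothesis. None of these uses T0.

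**Step 5: what a constant entered afterwards would do.** With a constant c at T0 the contrast becomes T2 − 2·T1 + c and moves one for one with c. A hypothetical example on the raw scale, with mean goal rating −1 at T1 and 0 at T2:

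- c = −2: 0 + 2 − 2 = 0
- c = −1: 0 + 2 − 1 = +1

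The same ratings give no effect or a positive one.

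**Step 6: what a change of anchor would do.** If the convention is built into the goal levels when they are written, changing it by s moves T0, T1 and T2 together. The coefficients are 1, −2 and 1, so s − 2s + s = 0 and the contrast does not change, apart from floor or ceiling effects. Step 5 therefore applies only to a constant unrelated to the written levels.

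**The case against.** The strongest reply is that the article leaves the T0 value unstated rather than showing that none exists. The sentence giving the −2 to +2 range is not limited to T1 onwards, and the scoring is referred to two cited sources. A starting level may have been fixed when each goal was written. The T1 rating would then already express change over the wait.

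Part of this stands. A level fixed by the goal descriptions at T0 is a usable score and should not be discarded because it varies little between participants. Nor do the documents support the stronger inference that a T0 level can never be recovered for those already enrolled.

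A reader might also infer that an arbitrary convention will decide the GAS result, and put a size on it. Under an assumed T-score with mean 50, SD 10, inter-goal correlation 0.3 and equal weights (none of them in the article), one scale level on every goal is worth 10·k/√(0.7·k + 0.3·k²) points for k goals: 10.0, 12.4 and 13.7 for one, two and three. Those figures illustrate an unanchored constant only. Nothing in the article says that one will be entered, and under a common re-anchoring the shift cancels (Step 6).

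The reply does not remove the conflict. Table 1 distinguishes goal setting from outcome rating, the text places evaluation at later visits, and the analysis section then requires a T0-to-T1 change for every primary outcome. These are two stated provisions that cannot both be followed, so this is more than detail left to a fuller document.

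**Conclusion.** The point holds. On the schedule and analysis as written, the waitlist-controlled CR effect cannot be estimated for GAS, one of three confirmatory outcomes. It should be resolved before analysis.

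The defect is confined to that contrast. A reader might infer that the primary objective as a whole fails. It does not: both ILSS outcomes are scored at T0 and T1, and the sample size rests on daily functioning. The active-versus-sham comparison on GAS is also intact.

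There is no numerical bias to report, because the article does not say what, if anything, would stand in for the T0 score. The conclusion assumes that Table 1 and the Goal attainment section describe the schedule actually followed. If T0 levels were in fact recorded, or fixed in the written goal levels, the repair is to say so and to state how they enter the model.

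**What to change.** 1. **From now on**, rate each goal's current level on the same −2 to +2 scale at T0 and compute a T0 T-score with the same weights. Preferably the same kind of assessor does this as at T1 to T3. Amend Table 1 and the Goal attainment section to match.
2. **For participants already past T0**, use a T0 level only if it was recorded, or fixed by the written goal-level descriptions, when the goals were set. State which. Do not enter an arbitrary constant afterwards.
3. **Where no such level exists**, pre-specify the GAS contrast as T2 versus T1, label it an uncontrolled pre-post change, and keep it out of the waitlist-controlled CR claim. State how GAS then stands in the Holm family.

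**Cost.** A brief extra rating at each T0 visit and a short change to the analysis text; treatment is not affected. The GAS claim becomes weaker for participants without a T0 level. At submission 126 − 59 = 67 participants of the planned total remained to be enrolled. If none of the 59 had a usable T0 level, the waitlist-controlled GAS analysis would rest on at most those 67, or about 53 after the plan's 20% dropout (67 × 0.8 = 53.6). Each further T0 visit without a rating or a fixed level lowers that number.

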##### Daily living skills

 The Independent Living Skills Survey (ILSS) measures the basic functional living skills and has acceptable psychometric characteristics [79, 80]. Both the Self-Report (ILSS-SR) and the Informant (ILSS-I, completed by the participants’ case manager) versions are utilised. The ILSS-SR comprises 70 items, nine of which are interviewer-rated, scored as yes, no, or not applicable. The ILSS-I includes 102 items rated from 0 (never) to 4 (always). Total scores are summed and averaged per domain, with higher scores indicating better performance.

#### Secondary outcome measures

Cognitive outcomes are assessed across multiple domains, with at least one test per MATRICS domain, except for social cognition, which is not targeted in this trial.

##### Processing speed

The Controlled Oral Word Association Test (COWAT) assesses verbal fluency and processing speed [81]. Participants must generate as many words as possible beginning with a specified letter within 60 s. Performance is the total number of words across three trials, and higher scores reflect better performance.

##### Attention, processing speed, and mental flexibility

The Trail Making Test (TMT) assesses visual search abilities, processing speed, and mental flexibility [82]. In version A, participants connect digits sequentially; in version B, digits and letters are alternated. Version B is relatively more challenging, as it also tests mental flexibility. Completion times are recorded, with longer times indicating lower performance.

##### Attention and working memory

The Digit Span forward task assesses immediate auditory attention [83]. The test administrator reads sequences of digits aloud, gradually increasing the length of each sequence, while participants repeat the digits in the same order. The score reflects the number of correctly recalled sequences, with a maximum score of 16 points. The Digit Span backward task assesses working memory, requiring participants to repeat the digits in reverse order, with a maximum score of 14 points [83]. In both versions, higher scores correspond to higher performance.

##### Visual memory

 The Visual Reproduction subtest of the Wechsler Memory Scale – Fourth edition (WMS-IV) assesses visual memory for abstract designs [84]. Participants are presented with five designs for 10 s each and reproduce them from memory. Each design is evaluated on different criteria, with a maximum score of 43 achievable. A recognition task involving the same designs is conducted after 30 min, with a maximum score of 5. Higher scores correspond with higher performance.

##### Verbal memory

 The 15-word learning task (WT-15) measures verbal memory [85, 86]. The test administrator reads a list of 15 words, and participants are asked to recall as many words as possible. This procedure is repeated five times, and the total number of correctly reproduced words constitutes the score. After 15–20 min, the delayed recall is administered, with a maximum score of 15. Higher values indicate higher performance on both immediate and delayed recall.

##### Executive functioning

 Subtasks of the Behavioural Assessment of the Dysexecutive Syndrome (BADS) assess executive functioning. First, the Key Search task assesses planning and organisation [87]. Participants are asked to plan a search route for an imaginary lost key within a field. Scores reflect whether the search strategy is systematic, efficient, and effective, and they receive deductions for slow responses. Second, the Dysexecutive questionnaire (DEX), a 20-item measure, evaluates metacognitive performance on executive functioning skills [87]. Both versions, filled in by participants and their case managers, are administered. Each question is scored between 0 (never) and 4 (very often). Higher total scores indicate worse performance on both subtasks.

